**7. TIMELINE**

**7.1. Visits and outcomes**

- Screening or baseline visit: The study investigator will offer to the eligible patients, who meet the inclusion criteria of the study and do not incur any of the exclusion criteria, to participate in the study; the patient information sheet and informed consent will be also given.

In this first visit or baseline visit, all the patients included in the trial will be evaluated and the following data will be registered in the CRF:

* Review of the inclusion and exclusion criteria of the study.

* Baseline evaluation on the VAS scale.

* Evaluation of the SF-12 scale of quality of life.

* Sociodemographic data (age, sex and origin of the patient).

* Concomitant diseases: any disease that is present at the beginning of the trial.

* Concomitant medication records: any medication the patient takes during the trial including the selection period. Any change in the concomitant medication must be recorded at each follow-up visit.

* Delivery of antiviral medication and gabapentin according to the dosage schedule established in the technical file. Every patient will be reminded that it must bring the medication bottle to the final visit.

-Visit 1 of treatment. Week 1

*The investigators will deliver to the included patients the antiviral and gabapentin medication or placebo, according to the dosing schedule established in the data sheet; instructions for trial capsule’ counting will be also provided, and the patient will be informed that he must register the intake of the study drug daily.

*Any new concomitant diseases not presented in the previous visit and any new prescribed medication will be recorded.

*Any adverse event will be registered, and the record information should include: description of the adverse event, start date, end date or if continuous, and the possible causality with the study drug.

-Visit 2 of treatment. Week 4

*The study investigator will prescribe the withdrawal of gabapentin or placebo, according to the technical data sheet; instructions for trial capsule’ counting for the withdrawal phase will be also provided, and the patient will be informed that he must register the intake of the study drug daily.

*Any new concomitant diseases not presented in the previous visit and any new prescribed medication will be recorded.

*Any adverse event will be registered, and the record information should include: description of the adverse event, start date, end date or if continuous, and the possible causality with the study drug.

-Visit 3 follow-up. Week 6.

*The researcher of the study will perform the study medication count and record the measure of adherence to treatment.

*It will evaluate the efficacy of short-term treatment, assessing the pain using visual analogue scale, the quality of life at 6 weeks using the SF-12 quality of life scale and it will record the quality of sleep using the MOS-Sleep scale.

*It will record the new concomitant diseases that have appeared and newly prescribed medication.

*Any new concomitant diseases not presented in the previous visit and any new prescribed medication will be recorded.

*Any adverse event will be registered, and the record information should include: description of the adverse event, start date, end date or if continuous, and the possible causality with the study drug.

Final follow-up visit. Week 12:

*The study investigator will evaluate the effectiveness of the treatment measuring the pain using a visual analogue scale.

*It will also evaluate the quality of life through the SF-12 scale of quality of life, the quality of sleep through the MOS-Sleep scale and will assess the patient neuropathic pain using the DN-4 neuropathic pain scale.

* Any new concomitant diseases not presented in the previous visit and any new prescribed medication, especially those prescribed for pain will be recorded.

*Any adverse event will be registered, and the record information should include: description of the adverse event, start date, end date or if continuous, and the possible causality with the study drug.

**7.2.** **Main dependent variable.**

Percentage of patients without PHN at the end of follow-up at 12 weeks (defined as score 0 on the Analog Visual Scale (VAS) of pain). The VAS scale will be used with a score of 0 to 10.

**7.3.** **Secondary dependent variables.**

- Percentage of patients without PHN at the follow-up visit at 6 weeks

- Percentage of patients without PHN at 6 weeks of onset of the acute condition defined as score 0 on the VAS scale of pain.

- Percentage of patients considered responders that improve the symptomatology of PHN at 6 and 12 weeks after the onset of the acute condition: We define responders to those patients who achieve a reduction of 50% or less on the VAS pain score. to basal.

·- Quality of life: using ShortForm-12 (SF-12 Spanish version ( [Med Care, 1996 Mar; 34 (3): 220-33.](https://translate.google.com/translate?hl=es&prev=_t&sl=auto&tl=en&u=http://www.ncbi.nlm.nih.gov/pubmed%3Fterm%3DMed%2520Care.%25201996%2520Mar%253B34%25283%2529%253A220-33.) ) ), a short form of SF-36® Heath Survey; all eight domains (physical functioning, role physical, bodily pain, general health, vitality, social functioning, role emotional and mental health) will be measured using a scale ranging from 0 to 100.,

- Sleep interference: the quality and quantity of sleep was measured by the Medical Outcomes Study Sleep Scale; this scale has been validated previously in Spanish and with 12 items, assessing the key constructs of sleep (Eur J Pain, 2007 Apr; 11 (3): 329-40.) In weeks 6 and 12,

-Patient with neuropathic pain by the Spanish version of the questionnaire DN4 (score on the scale > 3) (Health Qual Life Outcomes, 2007 Dec 4; 5: 66) , two-dimensional scale Pain quality and neurological exploration of the pain, which consists of 4 questions and 10 response items on the characteristics of pain .

- Impression scale of overall patient improvement  Spanish version ( [Int Urogynecol J Pelvic Floor Dysfunction, 2008 Aug; 19 (8): 1109-16](https://translate.google.com/translate?hl=es&prev=_t&sl=auto&tl=en&u=http://www.ncbi.nlm.nih.gov/pubmed%3Fterm%3D18360735) ) : consists of a single question that asks the patient to classify the relief obtained with the treatment that follows according to a Likert scale of seven points .

-Consumption of analgesics: In weeks 6 and 12 the analgesic consumption related to NPH will be evaluated.

All the variables of efficacy and quality of life will be collected through an interview with the patient.

- Security variable:

Incidence of adverse effects and severe AA. (sources: interview with the patient during follow-up visits to the study and clinical history of Primary Care).

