**3.2. Objectives and Hypothesis.**

1. **Main objective**

To evaluate the efficacy of an optimal dose of gabapentin added to the usual treatment -- valacyclovir and analgesics as needed -- in reduction of PHN at 12 weeks in patients more than 50 years-old who have moderate to severe pain.

Secondary objectives

To evaluate the efficacy of an optimal dose of gabapentin added to the usual treatment -- valacyclovir and analgesics as needed -- in reduction of PHN at 12 weeks in patients more than 50 years-old who have moderate to severe pain in terms of:

- Percentage of patients without PHN (defined as score 0 on the VAS scale of pain) at 6 weeks after the onset of acute symptoms.

- Percentage of patients with a reduction> 50% of the score on the VAS scale of pain at 6 and 12 weeks.

- Reduction of the incidence of neuropathic pain measured by the DN-4 scale.

- Improvement in the score of the SF-12 scale.

- To evaluate the safety of gabapentin treatment in terms of percentage of patient that report Adverse Events (AA).

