**5. SUBJECTS SELECTION**

**5.1. Inclusion and exclusion criteria**

**A) inclusion criteria**

To be included in the study, participants must meet all of the following inclusion criteria:

- Patients over 50 years old.

- Patients with uncomplicated HZ, within the first 72h since the rash onset, with moderate to severe pain (pain assessment on the VAS scale ≥ 4).

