**5.2. Sample size**

The sample size has been calculated according to the main efficacy variable. The percentage incidence of PHN in patients in the valaciclovir + placebo group is expected to be at least 45% (Helgason S, Petursson G, Gudmundsson S, Sigurdsson JA. Prevalence of postherpetic neuralgia after a first episode of herpes zoster: prospective study with long term follow up BMJ 2000 Sep 30; 321 (7264): 794-6.) and in the valaciclovir + gabapentin group of 20.3% ( Lapolla W, Digiorgio C, Haitz K, Magel G, Mendoza N, et al. incidence of postherpetic neuralgia after combination treatment with gabapentin and valacyclovir in patients with herpes zoster: open-label study Arch Dermatol 2011; 147 (8): 901-7 ), We have calculated a follow-up loss rate of 20%; an alpha risk of 5% and a beta risk of 20%. Therefore, it is necessary to recruit 134 patients (67 subjects in each treatment arm).

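### The responder definition in Protocol section 7.3 conflicts with the secondary objective in 3.2: in direction if read literally, and at exactly 50% even if read charitably

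*Protocol*

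**What the plan says.** The Protocol describes the pain-reduction endpoint in two places.

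- Section 3.2, secondary objectives: "Percentage of patients with a reduction> 50% of the score on the VAS scale of pain at 6 and 12 weeks".
- Section 7.3, secondary variables: the bullet opens with "Percentage of patients considered responders that improve the symptomatology of PHN at 6 and 12 weeks" and then gives the rule, "We define responders to those patients who achieve a reduction of 50% or less on the VAS pain score". A stray fragment referring to baseline follows the full stop.

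Three other provisions bear on it. Section 7.2 fixes the scale ("The VAS scale will be used with a score of 0 to 10") and defines freedom from PHN, the primary success, as "defined as score 0 on the Analog Visual Scale (VAS) of pain". The inclusion criteria in section 5.1 require moderate to severe pain at entry, "pain assessment on the VAS scale ≥ 4". Section 11 (statistical analysis) does not define a responder, and nothing else in the Protocol settles which version applies.

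**The concern.** Sections 3.2 and 7.3 describe the same endpoint at the same two time points, but the inequality points in opposite directions. The 7.3 rule also sits badly with its own bullet, which presents responders as patients who improve, and with the primary endpoint, because complete relief is the largest reduction possible.

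Two things are at stake. If the 7.3 sentence were carried unchanged into an analysis program, patients with complete relief would be counted as non-responders. And while two definitions stand side by side, the cut-point can be chosen after the data are known. This is not a detail left to a later analysis plan: the Protocol has already fixed the definition twice, and the two versions disagree.

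**Working it through.** **Inputs.** VAS range 0 to 10 (7.2); baseline VAS of at least 4 (5.1); primary success at VAS 0 (7.2); responder rules from 3.2 and 7.3. Percent reduction is taken as (baseline − visit)/baseline. It is defined for every eligible patient because the baseline is never 0. The Protocol does not say how finely the VAS is recorded, so whole-number scores are an assumption in the table.

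**Three readings.**

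- A, 7.3 as printed: a reduction above 0 and up to 50%. Unchanged scores are left out because the bullet speaks of improvement and of achieving a reduction.
- B, 3.2: a reduction above 50%.
- C, charitable reading of 7.3: a fall to 50% or less of baseline, that is, a reduction of at least 50%.

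**Visit scores that count as a response.**

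| Baseline | A: 7.3 as printed | B: 3.2 | C: charitable 7.3 | In C but not B |
| --- | --- | --- | --- | --- |
| 4 | 2–3 | 0–1 | 0–2 | 2 |
| 5 | 3–4 | 0–2 | 0–2 | none |
| 6 | 3–5 | 0–2 | 0–3 | 3 |
| 7 | 4–6 | 0–3 | 0–3 | none |
| 8 | 4–7 | 0–3 | 0–4 | 4 |
| 9 | 5–8 | 0–4 | 0–4 | none |
| 10 | 5–9 | 0–4 | 0–5 | 5 |

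**A against B.** The sets do not overlap at any baseline. This does not depend on whole-number scoring, since no reduction is both at most 50% and above 50%. From a baseline of 10, a visit score of 9 is a reduction of (10 − 9)/10 = 10%, a response under A only. A visit score of 0 is (10 − 0)/10 = 100%, a response under B only. Every primary success is a 100% reduction, so A excludes all of them.

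**C against B.** The direction now agrees. The difference is one score at each even baseline: 4 to 2, 6 to 3, 8 to 4 and 10 to 5, each a reduction of exactly 50%.

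**Sample size.** Section 5.2 bases the sample size on the primary variable, with PHN rates of 45% and 20.3%, 5% alpha (two-sided per section 11), 80% power and 20% loss. The unpooled normal formula reproduces the stated figure:

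n per arm = (1.960 + 0.842)² × (0.45 × 0.55 + 0.203 × 0.797)/(0.45 − 0.203)² = 52.66, rounded up to 53.

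53/0.80 = 66.25, rounded up to 67 per arm, or 134 in total. The responder rule does not enter this calculation.

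**The case against.** The strongest reply is that the reversal is only apparent. The Protocol reads as a translation, and the fragment after the sentence points to baseline. A reduction to 50% or less of baseline is a natural reconstruction, it agrees in direction with 3.2, and the bullet itself is about patients who improve. An attentive analyst would probably notice. This stands to the extent that the literal rule is unlikely to be the intended one. It does not remove the conflict, because the reconstruction includes exactly 50% and 3.2 excludes it.

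A reader might also infer three stronger claims that the document does not support.

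- **That unchanged patients count as responders.** Section 7.3 requires an achieved reduction and improvement, so this does not follow even from the literal text.
- **That the planning rates show an effective drug would look harmful.** With PHN of 20.3% on gabapentin and 45% on placebo, the patients not at VAS 0 cap the literal response at 20.3% and 45%. Two ceilings do not order the actual rates. If every gabapentin patient still in pain were a literal responder (20.3%), placebo would be lower whenever fewer than 20.3/45 = 45.1% of its patients still in pain were literal responders. Moreover, section 5.2 says the placebo rate "is expected to be at least 45" percent, so 45% is not a ceiling for placebo. These rates concern the primary outcome at week 12 and say nothing about week 6.
- **That 7.3 is what will be programmed.** The Protocol does not say so, and any statistical analysis plan was not available. Literal coding is a risk, not the expected result.

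**Conclusion.** The inconsistency is real and needs correcting. As printed, the 7.3 rule and the 3.2 objective select disjoint groups, and 7.3 classes every primary success as a non-responder. Under the more likely intended meaning, the disagreement shrinks to patients with exactly a 50% reduction. With whole-number scoring these can occur at baselines 4, 6, 8 and 10; how many there would be cannot be derived from the Protocol. A reversed treatment comparison is not established.

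The consequence is confined to one secondary endpoint, assessed at weeks 6 and 12. That the slip arose in translation is a judgement from the wording; the need for a single definition does not depend on it.

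**What to change.** Replace the responder sentence in 7.3, and align 3.2 with it, as follows: percent reduction = (baseline VAS − visit VAS)/baseline VAS; a responder is a patient with a reduction of more than 50% at the visit, assessed at weeks 6 and 12; a reduction of exactly 50% is not a response. This keeps the threshold already stated in the objective. If the team meant to include exactly 50%, both sections should say at least 50% instead. Delete the stray fragment after the sentence in 7.3.

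Make the change before unblinding, and carry the same wording into any statistical analysis plan. The cost is one sentence in 7.3 and a short clause in 3.2. No visit, measurement or recruitment target changes.

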  Although several pharmacological strategies are available for the treatment of PHN once it is established, its limited efficacy and the frequent occurrence of adverse effects make it necessary to search for therapeutic approaches during the acute phase of the infection to prevent its appearance. Given that severe pain during the acute phase of HZ is a risk factor for the subsequent development of PHN, one would expect that an optimal control of pain in this phase would be associated with a lower incidence of PHN.

Gabapentin is a neuromodulator whose analgesic effect in the treatment of pain in acute HZ and NPH is well established (16,17). It is also a drug with extensive experience of use and its benefit / risk balance and good tolerance is known; although it can cause various side effects, such as drowsiness, ataxia, diplopia, vertigo and nystagmus, they are very rare, mild and easily reverse by decreasing the dose or by making a progressive introduction; in addition, its interaction with other drugs is minimal, which facilitates its management. It is a drug that is not metabolized in the liver and eliminated by the kidney and barely binds to plasma proteins (less than 3%), therefore it has a good safety profile.  The penetration of the blood-brain barrier is quite good, which facilitates its analgesic action (18).

One of the key points for the treatment of HZ is the antiviral therapy within the first 72 hours after the onset of symptoms. In this sense, we believe that recruitment is more feasible in primary care practices. In our region (Balearic Island, Spain), the incidence of new cases of HZ diagnosed in primary care was 2200 cases in 2010, of which 1400 were aged 50 years or older.

The objective of this study of patients older than 50 years with moderate or severe pain from HZ is to assess the efficacy of gabapentin added to the usual treatment (valacyclovir and analgesics as needed) on reducing acute pain and preventing PHN at 12 weeks (19).

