**8. ADVERSE EFFECTS**

Incidence of adverse events and severe AA. In a double-blind study in patients with neuropathic pain treated with gabapentin, somnolence, peripheral edema and asthenia appeared in a higher percentage in patients> 65 when compared with younger patients. Apart from these facts, clinical investigations in this age group do not indicate different adverse events from that observed in young patients.

Despite this, as there have not been systematic studies in patients older than 65 years and the trial foresees the inclusion of patients older than 50 years, information regarding these AAs will be systematically collected. (Gabapentin, technical data sheet of the product).

When gabapentin was prescribed, several adverse effects have been detected, such as:

Disorders of blood and lymphatic system:

Common: leukopenia.

Rare: thrombocytopenia.

Immune system disorders:

Rare: allergic reactions (for example, urticaria).

Metabolism and nutrition disorders:

Common: anorexia, increased appetite.

Psychiatric disorders:

Frequent: hostility, confusion and emotional instability, depression, anxiety, nervousness, abnormal thinking.

Rare: hallucinations.

Nervous system disorders:

Very common: drowsiness, dizziness, ataxia.

Common: seizures, hyperkinesia, dysarthria, amnesia, tremor, insomnia, headache, sensations such as paresthesia, hypesthesia, abnormal coordination, nystagmus and increase, decrease or absence of reflexes.

Rare: movement disorders (for example, choreoathetosis, dyskinesia, dystonia).

Eye disorders:

Common: visual disturbances such as amblyopia, diplopia.

Ear and labyrinth disorders:

Common: vertigo.

Rare: tinnitus.

Cardiac disorders:

Rare: palpitations

Vascular disorders:

Common: hypertension, vasodilation.

Respiratory, thoracic and mediastinal disorders:

Common: dyspnea, bronchitis, pharyngitis, cough, rhinitis.

Gastrointestinal disorders:

Common: vomiting, nausea, dental anomalies, gingivitis, diarrhea, abdominal pain, dyspepsia,

constipation, dry mouth or throat, flatulence.

Rare: pancreatitis.

Hepatobiliary disorders:

Rare: hepatitis, jaundice.

Disorders of the skin and subcutaneous tissue:

Common: facial, purple edema most often described as contusions resulting from physical trauma, rash, pruritus, acne.

Rare: Stevens-Johnson syndrome, angioedema, erythema multiforme, alopecia.

Musculoskeletal and connective tissue disorders:

Common: arthralgia, myalgia, back pain, spasms.

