- Final comparative analysis: Comparison of the clinical characteristics, of medication between the groups of placebo and treatment, using t-test and chi-square test. If the normality assumptions are not met, nonparametric tests will be applied. The clinical relevance of the intervention will be determined from the absence of pain at 12 weeks in the control and intervention groups and in the benefit / risk ratio of the intervention, the relative risk reduction (RRR), the absolute risk reduction (ARR) and the number of patients needed to treat will be calculated (NNT). A crude analysis will be performed by chi-square and adjusted by logistic regression of the baseline characteristics that show to be different in the control and intervention groups. All the analyzes will be carried out by intent to treat (`intention to treat '). The level of statistical significance is established at 5% bilaterally.

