**12. DIFFICULTIES AND LIMITATIONS OF THE STUDY.**

  When including patients with moderate or intense pain, an effect of regression to the mean could occur, therefore there would be a tendency for these patients to refer less intense pain independently of the effect of gabapentin or placebo; however when comparing two groups we assume that this effect will occur in the two groups equally and therefore will not affect the estimation of the magnitude of the risk.

Gabapentin is a drug that can have adverse effects, and this may cause on one hand, a greater number of losses of follow-up in the active drug group; if these losses are more frequent in older patients, with more comorbidity or greater immunosuppression, a type I error can occur; to avoid it we opted for an intention-to-treat analysis.

On the other hand, patients taking the active drug could recognize that they are not taking placebo due to the presence of such adverse effects; to control the possible lack of blinding of the collaborating GP doing the follow-up visits and the patients, the number follow-up visits have been limited. The magnitude of the masking of the placebo will be assessed both in patient and collaborating GP; they will be asked to which treatment group they think belong.

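### The primary pain score is collected by interview by the same role that manages study drug and records adverse events: an avoidable, unquantified risk of bias at a cut-off of exactly 0

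*Protocol*

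**What the plan says.** **Mode of collection.** Section 7.3: "All the variables of efficacy and quality of life will be collected through an interview with the patient". The sentence stands under the secondary variables but speaks of all efficacy variables. Section 7.1 has the investigator take the primary measure at week 12: "The study investigator will evaluate the effectiveness of the treatment measuring the pain using a visual analogue scale".

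**Endpoint.** Section 7.2 counts a patient as free of PHN only at a score of 0 on a 0 to 10 scale.

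**Who does what.** In section 7.1 the investigator delivers the study drug, prescribes its withdrawal at week 4, counts capsules at week 6, and records adverse events with possible causality at weeks 1, 4, 6 and 12. The visit table in section 13 names the investigator, and nobody else, at all five visits. Section 10.2 gives the same role the periodic evaluation. Section 12 calls this person the collaborating GP who does the follow-up visits.

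**Masking.** Section 4.3 masks investigator, patient and statistician, and asks each to guess the arm without saying when. Section 12 accepts that adverse effects may let patients recognise active drug, and answers: "to control the possible lack of blinding of the collaborating GP doing the follow-up visits and the patients, the number follow-up visits have been limited". It also relies on the guess question.

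**Frequency of revealing effects.** Section 8 lists "Very common: drowsiness, dizziness, ataxia". Section 3.1 names drowsiness and ataxia among side effects and says "they are very rare, mild and easily reverse by decreasing the dose".

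**The concern.** The step from a low score to 0 decides the primary outcome, and it is a subjective rating given in conversation. If the person asking has formed a view of the arm from tolerability during dosing, or the patient has and wants to please, some low scores may be recorded as 0. If this happens more often on gabapentin, the error is differential and produces an apparent benefit on the primary endpoint, the responder rate and SF-12.

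The two measures in section 12 do not reach this. Fewer visits may reduce exposure, but the week-1 and week-4 visits, where adverse events are recorded, both precede the efficacy interviews at weeks 6 and 12. The guess question records a belief; it does not shield the score. A guess taken at the end may also reflect how the patient's pain went, so it cannot by itself show unmasking. No analysis can repair a score recorded this way.

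**Working it through.** **1. The plan's own figure.** Inputs from section 5.2: 45% PHN on placebo, 20.3% on gabapentin, alpha 5%, power 80%, loss 20%. Section 11 makes the test two-sided: "The level of statistical significance is established at 5% bilaterally". With the unpooled formula:

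n = (1.96 + 0.8416)² × (0.45 × 0.55 + 0.203 × 0.797) / (0.45 − 0.203)² = 7.849 × 0.4093 / 0.0610 = 52.7, so 53 per arm.

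53 / 0.8 = 66.25, so 67 per arm and 134 in total, as stated. The sample size is not in question; 53 is the evaluable number used below.

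**2. What a leak would do.** The documents give no rate, so every leak size here is an assumption. Suppose gabapentin has no effect and true PHN is 45% in both arms. Recorded PHN on gabapentin is then 0.45 − d, where d is the spurious shift. For the two-sided 5% chi-square test (normal approximation):

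P(reject) = Φ[(d − 1.96 s₀)/s₁] + Φ[(−d − 1.96 s₀)/s₁]

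Here s₀ = √[2p̄(1 − p̄)/n], s₁ = √[p₁(1 − p₁)/n + p₂(1 − p₂)/n], and p̄ is the mean of the two recorded rates.

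Two ways to set d:
- *Two-step:* d = 0.45 × g × f, where g is the excess share of gabapentin patients with residual pain whose arm is guessed, and f is the share of those then recorded as 0.
- *Direct:* d = 0.45 × c, where c is the share of all non-zero gabapentin scores recorded as 0.

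| Assumption | d (points) | False-positive rate, 53 per arm |
|---|---|---|
| no leak | 0 | 5.0% |
| g = 20%, f = 10% | 0.9 | 5.1% |
| g = 40%, f = 20% | 3.6 | 6.6% |
| c = 10% | 4.5 | 7.5% |
| g = 60%, f = 30% | 8.1 | 13.5% |
| c = 20% | 9.0 | 15.6% |

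Worked line for 9 points: p̄ = 0.405, s₀ = 0.0954, s₁ = 0.0950. The first term is Φ(−1.02) = 0.154 and the second Φ(−2.92) = 0.002, together 0.156.

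**3. Timing.** Table 1 titrates over days 1 to 7, and adverse events are first recorded at week 1. Section 3.2 puts the primary assessment after 5 weeks of treatment and 7 without. At week 12 a leak can therefore run only through remembered effects; at week 6 the gap is about one week.

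**4. The frequency statements.** Section 3.1 calls drowsiness, ataxia, diplopia, vertigo and nystagmus very rare. Section 8 puts drowsiness and ataxia under very common, and diplopia, vertigo and nystagmus under common. All five disagree, and the unmasking risk depends on which set applies.

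**The case against.** The strongest case against runs as follows.

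- **Order.** Section 7.1 already lists the VAS before adverse events at weeks 6 and 12. That stands as a mitigating point. But a list is not a rule, and at week 6 the VAS comes after the capsule count.
- **Meaning of interview.** The protocol also uses the word to name a data source, as against the clinical history. It does not say that the GP reads out or marks the scale, and a VAS is by nature a patient rating. The investigator's manual, which is not shown, may settle this. That is fair, and a reader should not infer that the GP scores the pain. Still, self-completion is stated nowhere. Section 1.11 speaks of an average daily score, but no pain diary appears in the visit schedule.
- **Masking and time.** Both parties are formally masked, and 7 weeks off drug weakens the route to the primary score. Both points stand and limit the weight of the concern.
- **One arm only.** A reader might infer that revealing effects occur only on gabapentin, so the error must favour it. The documents do not support this: section 8 gives no placebo rates, and section 6 allows opioids in both arms. How well symptoms separate the arms is unknown.
- **Same person.** That one individual does everything for a patient is inferred from the role named at each visit. No passage names a separate assessor.

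**Conclusion.** The concern holds as an avoidable risk of bias in how the primary score is collected. A reader might go further and conclude that the trial's result would be biased towards gabapentin; the documents do not show that.

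The size is illustrative. Under no true effect, 45% PHN in both arms and 53 evaluable per arm, a shift of about 1 to 9 points takes the false-positive rate from 5% to between about 5% and 16%. The low end is practically nominal. The high end needs one in five non-zero gabapentin scores to be recorded as 0 and none on placebo.

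What justifies acting is the combination of a cut-off at exactly 0, an unmasking risk that the protocol itself concedes, safeguards that do not separate the rating from that knowledge, and a very low cost of change. The disagreement between sections 3.1 and 8 is editorial.

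**What to change.** - **Sections 7.1 and 7.3:** state that the patient completes VAS, SF-12 and MOS-Sleep alone on paper at the start of the week-6 and week-12 visits, before the capsule count and before any question on adverse events, medication or treatment guess. The GP checks completeness only. DN4 stays with the investigator because it includes an examination.
- **Section 4.3:** say when the guess is asked, and place it after the efficacy forms.
- **Section 12:** say that fewer visits may reduce unmasking but do not control it.
- **Sections 3.1 and 8:** reconcile the adverse-effect frequencies.

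Cost: the order of CRF pages and a line in the investigator's manual. No extra visit or staff, and no change to the sample size. Patients who cannot complete a form alone will need neutral help, flagged in the CRF. The change closes the interviewer route only; the patient's own belief about treatment remains.
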